### Statistical analysis

3.7

The data will be analyzed using the Statistical Package for the Social Sciences version 22.0 (SPSS 22.0, Chicago, IL). The qualitative data is analyzed by descriptive statistics, expressed by frequency and percentage; the measurement data is expressed as mean ± standard deviation and tested by *t* test or *q* test. Chi-square test is used for counting data. Spearman correlation analysis is used for single factors and logistic regression analysis is used for multiple factors. The composition ratio data is tested by *x*^2^ test. Unidirectional ordered data were tested by rank sum test. All statistical tests will be bilateral tests and *P*-values < .05 is considered to indicate statistical significance.

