**Methods::**

A prospective, open-label, randomized, placebo-controlled clinical will be performed. A total of 60 patients diagnosed with UA will be randomly allocated to either the treatment group or the control group with a 1:1 ratio. The participants in the treatment group will receive LFN-G treatment and the participants in the control group will receive placebo. Meanwhile, both groups continue to undergo standard western medicine treatments. The duration of interventions is 4 weeks. The primary endpoint is the incidence of major cardiac adverse events, defined as a composite of recurrent angina, acute myocardial infarction (AMI), severe arrhythmia, heart failure, and cardiac death. Secondary outcomes include Seattle angina scale score, Chinese medicine syndromes and electrocardiograph (at weeks 0, 1, 2, 4), myocardial nuclides perfusion, measurement of wall motion score index and left ventricular ejection fraction, serum inflammation factors such as C-reactive protein, high sensitive-C-reactive protein, interleukin-6, matrix metalloproteinase-9, and so on (at weeks 0, 4). In addition, some biochemical indexes of blood and hematological indexes will be used to assess the safety of treatments. Any adverse effects of the treatment will be recorded.

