### Outcome measures

3.3

Primary outcome is the incidence of major cardiac adverse events, defined as a composite of recurrent angina, acute myocardial infarction, severe arrhythmia, heart failure, and cardiac death. This outcome will be compared with the baseline and the 4th week.

Secondary outcomes including:

(1)Seattle angina scale score: This score includes 4 aspects (physical activity limitation, angina frequency, treatment satisfaction, and disease cognition) and it can provide information of participants’ subjective assessment of therapy. This outcome will be compared the baseline with the 1st, 2nd, 3rd, and 4th week.(2)Chinese medicine syndromes: This outcome will be compared the baseline with the 1st, 2nd, 3rd, and 4th week.(3)ECG: The change of St-segment and T wave of baseline and the 1st, 2nd, 3rd, and 4th week.(4)Myocardial nuclides perfusion: It will be used to evaluate myocardial perfusion under endocardium and epicardium of the baseline and the 4th week.(5)Echocardiography: Measurement of wall motion score index and left ventricular ejection fraction of the baseline and the 4th week.(6)Vitro measurement: Measurement of serum inflammation factors such as C-reactive protein, high sensitive-C-reactive protein, interleukin-6, matrix metalloproteinase-9, and so on.

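### Section 3.7 assigns continuous secondary outcomes to a t or q test, which gives up the precision of the measured baseline and leaves weekly scores without a single named test

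*Protocol article*

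**What the plan says.** **Test.** Protocol article, section 3.7 (Statistical analysis): "the measurement data is expressed as mean ± standard deviation and tested by" a t test or a q test. Two sentences there apply to every test: "All statistical tests will be bilateral tests", and P-"values < .05 is considered to indicate statistical significance". The only regression model named is logistic ("logistic regression analysis is used for multiple factors"), which does not fit a continuous outcome. Unidirectional ordered data go to a rank sum test.

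**Visits.** Section 3.3 (Outcome measures) says of the Seattle score, and again of the Chinese medicine syndromes, "This outcome will be compared the baseline with the 1st, 2nd, 3rd, and 4th week". The ECG has the same four weeks. The Abstract differs: "Secondary outcomes include Seattle angina scale score, Chinese medicine syndromes and electrocardiograph (at weeks 0, 1, 2, 4", which is three post-baseline visits. Echocardiography and perfusion are measured at baseline and week 4. The serum outcome is given in section 3.3 as "Measurement of serum inflammation factors such as C-reactive protein, high sensitive-C-reactive protein, interleukin-6, matrix metalloproteinase-9" and others, without dates; the Abstract dates it at weeks 0 and 4.

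**Size.** "A total of 60 patients diagnosed with UA will be randomly allocated to either the treatment group or the control group with a 1:1 ratio", so 30 per arm.

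**The concern.** The data contain more information than the stated test uses. Patients who start with a poor score or a low ejection fraction tend to finish with one, and a baseline-adjusted model removes that part of the between-patient variation. A t test of week-4 values leaves all of it in. A t test of changes removes it only partly.

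For the weekly scores there is a second problem. The article names no principal visit and no joint model, and applies .05 to every test. Taken as written, each score gives three or four chances of a significant week.

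The q test is a procedure for comparing three or more means, and this trial has two arms. If it were applied across visits instead, it would treat repeated values from one patient as independent.

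The stake is moderate. These are secondary outcomes, but the Discussion relies on the angina score and on objective indicators, and makes a promising result the reason for a larger trial. Lost precision can hide an effect, and one favourable week can be read as success.

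**Working it through.** **Inputs from the article:** 30 per arm, two-sided 0.05, visits as listed above. **Assumed, because the article does not give them:** the baseline to week-4 correlation r (0.3 to 0.7), the inter-visit correlation (0.5 to 0.9), 80% power, and differences expressed in SD units. The article states no effect size, SD or power, so it has no precision figure to reproduce.

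**Step 1: precision.** Variance of the between-arm difference relative to a week-4 t test, with equal SD at both times:

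- week-4 t test: 1
- change-score t test: 2(1 − r)
- ANCOVA: 1 − r²

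Detectable difference for the week-4 t test: (1.96 + 0.84) × √(2/30) = 0.72 SD. The other methods multiply this by the square root of their relative variance.

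| r | ANCOVA variance | Change-score variance | Detectable, ANCOVA | Detectable, change score |
|---|---|---|---|---|
| 0.3 | 0.91 | 1.40 | 0.69 SD | 0.86 SD |
| 0.5 | 0.75 | 1.00 | 0.63 SD | 0.72 SD |
| 0.7 | 0.51 | 0.60 | 0.52 SD | 0.56 SD |

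Power for an assumed difference of 0.5 SD is 49% with the week-4 t test, and 53%, 61% and 77% with ANCOVA at r = 0.3, 0.5 and 0.7.

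In patients, against a change-score t test: at r = 0.5, 60 × 1.00/0.75 = 80; at r = 0.7, 60 × 0.60/0.51 ≈ 71. These are large-sample factors and ignore the degree of freedom spent on the baseline term.

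**Step 2: false positives for the weekly scores.** If the visits were independent, the chance of at least one P < .05 would be 1 − 0.95⁴ = 18.5% for four visits and 1 − 0.95³ = 14.3% for three. Visits in one patient are correlated, so the rate was simulated: 60,000 null trials per setting, 30 per arm, equal correlation between visits, one t test per visit.

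| Inter-visit correlation | Four visits (section 3.3) | Three visits (Abstract) |
|---|---|---|
| 0.5 | 16.0% | 12.5% |
| 0.7 | 13.3% | 10.8% |
| 0.8 | 11.5% | 10.1% |
| 0.9 | 9.3% | 8.5% |

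If change scores are tested instead, and all visits including baseline share one correlation r, two changes have covariance 1 − r and variance 2(1 − r). Their correlation is therefore (1 − r)/[2(1 − r)] = 0.5 whatever r is, and the first row applies.

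**The case against.** **The detail may be in an analysis plan that is not shown.** This holds for what the article is silent on, such as a multiplicity rule, and that silence is not the finding. But section 3.7 does not leave the test open: it names one, and an analysis plan that followed it would carry the same choice.

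**The unadjusted test is not wrong.** This stands. A reader might infer that chance baseline imbalance biases the comparison. Under randomisation the between-arm t test is unbiased and keeps its error rate, and imbalance is ordinary sampling variation already in the standard error. The loss is one of precision.

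**Section 3.3 may already use the baseline.** Comparing baseline with later weeks may well mean change scores. This stands, and it limits the size. Against a week-4 t test, ANCOVA at r = 0.7 would be worth 60/0.51 ≈ 118 patients, but that figure needs a reading which the text does not establish; against a change score it is about 71. A third reading, before-after tests within each arm, would not compare the arms at all.

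**Visit-by-visit testing is an inference.** In part this stands. The article does not spell it out, but it names comparisons at each week, one threshold for every test and no principal visit. A reader might extend the inflation to all continuous outcomes, or take the visits for interim analyses. Neither is supported: LVEF, wall motion score index and serum markers have one follow-up time, and the weekly visits are outcome assessments.

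**Outcome types are not all stated.** This stands. No numeric syndrome score is defined, and syndrome grades may belong to the rank sum test. A reader might also infer that the serum markers are skewed and must be analysed on a log scale; the article gives no distribution, so that is not claimed here.

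**Conclusion.** The point holds as an avoidable inefficiency together with an unprotected set of weekly tests, not as an invalid analysis. The precision gain depends on a correlation that the article does not give. Against a week-4 t test, ANCOVA removes 9% of the variance at 0.3, 25% at 0.5 and 49% at 0.7. Against a change score it removes 25% at 0.5 and 15% at 0.7 (1 − 0.51/0.60). ANCOVA is never the less precise of these methods beyond the degree of freedom it spends.

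The error rate of about 16% to 11% over four visits (correlation 0.5 to 0.8), or 12.5% to 10.8% over three (0.5 to 0.7), concerns the Seattle score, and the syndrome outcome only if it is scored numerically. It assumes that each visit is tested at .05.

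Two parts need no assumption: the q test has no use for two arms at one visit, and the Abstract and section 3.3 disagree on the visits. The primary outcome is untouched, so this should be changed but is not critical.

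**What to change.** In section 3.7, replace the t test or q test for continuous secondary outcomes with:

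- **LVEF, wall motion score index, serum markers:** ANCOVA of the week-4 value on arm and baseline value.
- **Weekly continuous scores:** one mixed model for repeated measures with arm, visit, arm-by-visit and baseline. The week-4 between-arm contrast is the single reported test, and other visits are shown as estimates with confidence intervals.
- **q test:** delete.

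Reconcile the assessment weeks in the Abstract and section 3.3, and state whether the syndrome outcome is a numeric score or an ordered grade, since this decides which method applies. Add the stratification factors of section 2.4 (age, sex, morbid status, comorbidities) as covariates only as far as their levels are defined and few enough for 60 patients.

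Cost: wording, slightly more analysis work and a few degrees of freedom. No additional data or visits are needed.

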## Discussion

4

UA is a common manifestation of coronary artery disease that seriously affects the quality of life and causes deaths and potential years of life lost. Current treatments for UA are still not satisfy all clinical conditions. There is a wide acceptance of CHM for treating coronary artery disease in China and it has obvious curative effect indeed. In a long-term clinical work of our team, we have found the efficacy and safety of LFN-G in treatment of UA. But we need a compelling RCT evidence to further demonstrate the benefits and risks of adding LFN-G to the standard western medicine treatment for patients with UA.

In order to evaluate the efficacy and safety of LFN-G, we design this prospective, open-label, randomized, placebo-controlled trial. In this trial, we focus on the incidence of major cardiac adverse events, angina score, quality of life, and utilize some objective physical and chemical indicators to ensure the reliability and generality of the results.

There exist some limitations to this study. First, this is a single-center, small scale RCT. Second, the follow-up duration is relatively short. Third, this trial will be performed in Beijing, China, there may be regional and ethnic deviations. Thus, if we finally get a promising result from this current, we consider conducting a multicenter, randomized, large scale, and long follow-up trial in order to provide more significant information to guide clinical treatment.
